#### Spillover effects

An effective intervention must decrease or interrupt transmission among individuals receiving the intervention (a “direct effect”) as well as among non-recipients outside of intervention zones (a “spillover effect” or “community effect”) [75–77]. There is a biological basis for spillover effects of fMDA. Chemotherapy can block transmission by reducing gametocyte biomass, and subsequent movement of humans and mosquitos can result in spillover effects outside of intervention zones. Our primary analysis at the cluster level is a pooled effect estimate across intervention recipients and non-recipients. Direct and spillover effects of fMDA will be estimated by comparing malaria incidence and prevalence in non-recipients in proximity to fMDA zones by arm. Direct effects will be defined as the cumulative incidence ratio (or prevalence ratio) among treated individuals in focal treatment zones within 200 meters of index case in the intervention arm vs. the control arm. Spillover effects will be defined as the cumulative incidence ratio among treated individuals outside focal treatment zones around index cases in the intervention arm vs. the control arm. To test for possible contamination of the control arm, using data from the endline prevalence survey, we will assess whether malaria prevalence in the control arm differs between households closer to or further from treatment clusters. We will calculate the distance from each household sampled in the endline survey to the nearest treatment cluster boundary. Then we will perform a clustered permutation test of the null hypothesis that malaria incidence and prevalence do not differ at the 20th and 80th percentiles of the distance to the nearest treatment cluster boundary, controlling for covariates used in the constrained randomization [78].

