#### fMDA in the intervention arm

In the intervention arm, fMDA will be administered over 3 consecutive years. In each cycle, the intervention arm will receive two rounds of fMDA, with each round separated by 2 months and each cycle separated by 9–11 months (Fig. 4). fMDA will be administered by directly observed therapy (DOT) and will target high-risk individuals meeting eligibility criteria detailed in Table 1. These eligibility criteria include being a malaria index case or living in a household within a 200-meter radius of a *P. vivax* index case. The 200-meter radius was selected based on evidence from other cohort studies in the Peruvian Amazon indicating clustering of asymptomatic, submicroscopic infections among neighboring households, generally within 200 meters [33–35]. Index cases will include cases reported in the 2 years prior to the first round of each fMDA cycle detected through passive or active case detection. Individuals with high-risk status will be screened for other inclusion and exclusion criteria for fMDA eligibility.

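### The spillover effect is defined in treated people outside the zones, contradicting the protocol's own targeting rule, and the direct effect has no stated comparison group in the control arm

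*Protocol article*

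**What the plan says.** The Spillover effects section of the protocol article names the population for these effects in four places.

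- **Concept.** Spillover occurs "among non-recipients outside of intervention zones", and a direct effect occurs in those who receive the intervention.
- **Estimation.** "Direct and spillover effects of fMDA will be estimated by comparing malaria incidence and prevalence in non-recipients in proximity to fMDA zones by arm".
- **Direct effect, formal definition.** A cumulative incidence (or prevalence) ratio "among treated individuals in focal treatment zones within 200 meters of index case in the intervention arm vs. the control arm".
- **Spillover effect, formal definition.** "Spillover effects will be defined as the cumulative incidence ratio among treated individuals outside focal treatment zones around index cases in the intervention arm", again against the control arm.

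Under fMDA in the intervention arm, drug delivery "will target high-risk individuals meeting eligibility criteria detailed in Table 1". High risk there means being an index case or living within 200 m of one. Index cases are those of the two years "prior to the first round of each fMDA cycle detected through passive or active case detection". Table 1 adds presence at delivery, consent or assent, G6PD and hemoglobin limits, no pregnancy and no recent antimalarial.

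The Secondary analyses section plans g-methods to handle non-adherence, but states them for the per-protocol analyses. The Spillover effects section also says that the primary cluster-level analysis pools recipients and non-recipients.

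**The concern.** There are three problems with these definitions.

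1. The operative spillover definition names people who were treated and live outside the zones. The targeting rule is meant to produce no such people, and the opening of the same section assigns spillover to the untreated.
2. The estimation sentence places both effects in non-recipients. A direct effect cannot be estimated in people who did not take the drug.
3. The direct-effect contrast takes people who ended up treated in one arm and sets them against the control arm, where nobody was treated. Whether someone is treated is settled after randomization, by presence, willingness and clinical eligibility. No corresponding control group is named, so randomization does not protect the comparison.

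The section itself holds that an effective intervention must work both in recipients and beyond them. As written, the first effect is open to selection bias and the second has no usable population. If the groups are chosen only when data are in hand, both results become post hoc.

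**Working it through.** **The plan's own figure.** The protocol gives no power or precision for direct or spillover effects. Its only design figure is for the primary outcome: 80% power for a 68% reduction with 15 clusters per arm. Inputs are λ0 = 0.065, λ1 = 0.32 × 0.065 = 0.0208, k = 0.87 and y = 251 × 3 = 753 person-years per cluster. The usual cluster rate formula is

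c = a + (1.96 + 0.84)² × [(λ0 + λ1)/y + k²(λ0² + λ1²)] / (λ0 − λ1)²

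The ratio after the squared term is (0.000114 + 0.003525)/0.001954 ≈ 1.863. This gives c = 14.6 with a = 0 and 15.6 with a = 1. Power with 15 clusters is 81.0% or 78.3% respectively. The stated figure reproduces, and nothing below touches it.

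**Who is in the spillover group as defined.**

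| Statement | Received drug? | Location |
|---|---|---|
| Concept sentence | No | Outside zones |
| Estimation sentence (both effects) | No | Near zones |
| Direct effect, formal | Yes | Inside zones |
| Spillover, formal | Yes | Outside zones |
| Delivery rule and Table 1 | Offered only to index cases and those within 200 m of one | Inside zones |

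The fourth row conflicts with the first and the last. The people who could fall into it are exceptions: someone dosed off protocol, someone who moved, or someone treated in an early cycle whose qualifying case later passed out of the two-year window. All of them took the drug, so their incidence carries its effect on themselves. The group is essentially empty or incoherent, and in neither case does it measure spillover.

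**Direct effect with an inert drug.** The documents give neither uptake nor the relative risk of takers and non-takers, so both are assumed and varied. Let c be coverage among in-zone residents and r the risk of treated relative to untreated in-zone residents, with no drug effect. Average in-zone risk is then proportional to c·r + (1 − c). Against all control-arm residents of equivalent zones,

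CIR = r / (c·r + 1 − c)

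| | c = 0.6 | c = 0.8 |
|---|---|---|
| r = 0.6 | 0.6/0.76 = 0.79 | 0.6/0.68 = 0.88 |
| r = 1.4 | 1.4/1.24 = 1.13 | 1.4/1.32 = 1.06 |

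An inert drug could look 12–21% protective or 6–13% harmful. If the comparator were the whole control arm, the CIR would also be multiplied by the ratio of in-zone to whole-arm risk. On the protocol's premise that zone residents are at higher risk, that pushes the CIR upward. The documents do not settle the sign of r − 1. Potential challenges expects people to be away in the field, to sleep in several homes or to live mostly in Iquitos, and such people may have more or less exposure than those reached.

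**A check on the one-word repair.** Changing treated to untreated would restore the concept but restrict only one arm. Delivery zones move with each cycle, so residents outside the launch zones who later gain a nearby case may be treated and so leave the untreated group, in the intervention arm only. If 20% left with twice the incidence of those remaining (assumed), the rest would have 1/(0.8 + 0.2 × 2) = 0.83 of the average. That is an apparent 17% spillover benefit from an inert drug.

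**The case against.** The strongest reply is that this is a slip. The section points to non-recipients twice before the faulty sentence, so a sensible analyst would read untreated. Direct and spillover effects are not among the secondary outcomes listed under Aims and objectives, and a condensed article may leave the construction of comparators to a fuller plan. The material for a fair comparison also exists: cases across the study area are to be geolocated, and G6PD activity and hemoglobin are measured before any intervention.

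Much of this stands. It limits the seriousness and makes the repair easy. It does not remove the point, because the faulty sentence is the one that defines the effect, the estimation sentence is wrong for direct effects, and the one-word change brings its own selection. Willingness and presence at dosing also cannot be observed in controls, however well measured eligibility is matched.

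A reader might infer three stronger things that the text does not support.

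- **That direct effects compare recipients with everyone in the control arm.** The comparator is undefined. The wording can also be read as equivalent zones in both arms.
- **That the analysis zones are redrawn each cycle and so shrink in the intervention arm if fMDA works.** The protocol updates zones for delivery. It does not say which zones the analysis uses.
- **That this undermines the case for focal over village-wide treatment.** The trial compares fMDA with no fMDA and has no village-wide arm.

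**Conclusion.** The point holds as a defect in the definitions of two secondary analyses. The spillover definition contradicts its own section and the targeting rule. The estimation sentence cannot give a direct effect. The direct-effect contrast compares a group selected after randomization with an unspecified control group, and no adjustment is stated for it.

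The size of the direct-effect bias is not known. The ranges of 0.79–0.88 and 1.06–1.13 rest on assumed coverage of 60–80% and assumed relative risks of 0.6 and 1.4, with equivalent zones as comparator. A reader might choose one setting, such as 75% uptake and doubled risk in the untreated (1/(0.75 + 0.25 × 2) = 0.80), and conclude that the plan builds in a 20% false benefit. The documents do not support a single figure or a direction.

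Nor should the spillover group be called strictly empty, since a few treated people may fall outside a later zone. The primary ITT comparison and its power are unaffected.

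**What to change.** Amend the Spillover effects section, and the analysis plan to match, before outcome data are examined by arm.

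1. **Zones for analysis.** Draw 200 m zones once, by the same rule in both arms, around the geolocated index cases of the two years before launch.
2. **In-zone effect.** CIR by randomized arm among all residents inside these zones who meet the eligibility criteria measured at baseline in both arms (for example age, G6PD activity and hemoglobin), regardless of uptake.
3. **Spillover effect.** CIR by randomized arm among all residents outside these zones, without restricting to the untreated.
4. **Effect in actual recipients.** Supplementary only, with the adjustment stated, for example by extending the planned g-methods to this contrast.
5. **Wording.** Delete or correct the estimation sentence that places both effects in non-recipients, and remove treated from the spillover definition. The concept sentence can stay.

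The cost is wording and some mapping. Study setting and trial preparations already plans to collate and geolocate pre-launch cases across the study area, and the baseline assessment already records G6PD activity and hemoglobin.

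The downside is that launch zones do not follow later targeting. Some residents outside them will be treated in later cycles, so the outside-zone contrast will carry some direct effect. Report the share treated, and give a cycle-updated version as a descriptive supplement.

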#### Safety and tolerability analysis

Serious adverse events refer to any expected or unexpected event, related or unrelated to the study medication, that results in death, a life-threatening event, hospitalization, prolongation of hospitalization, disability or incapacity, or a congenital anomaly. The incidence of serious adverse events (SAE) from fMDA, defined as SAEs divided by person-time at-risk, will be measured. Sub-analyses will be conducted by drug type. The incidence of SAE or severe malaria in fMDA will also be compared to the incidence of severe malaria in the control arm [79–82]^.^ AEs and adherence will also be assessed descriptively.

Lack of drug tolerability will be assessed as missed doses of study drugs due to vomiting or non-adherence due to adverse effects. Adverse event monitoring will be conducted both actively and passively.

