#### Safety

Adverse events (AE) include any unfavorable or unintended sign, symptom, disease, syndrome, abnormal laboratory finding, or illness that emerges or worsens relative to each participant’s pre-treatment baseline, whether or not it is connected to the study intervention. Study clinicians will assess and grade all AEs based on the DAIDS severity grading scale [53]. AEs will be monitored passively, by participant calls to study staff or visits to a local health facility, and actively, through study staff who will actively inquire about AE at monthly visits.

Lack of drug tolerability will be assessed as missed doses due to vomiting or non-adherence due to adverse effects. An AE of special interest (AESI) in this study is 8-aminoquionline-associated hemolysis which is known to occur in individuals with G6PD deficiency and with malaria itself. Monitoring for this AESI and other adverse reactions will be conducted through passive and active surveillance being conducted in both study arms. Additionally, active pharmacovigilance will occur as study staff inquire about symptoms among during return visits to complete treatment. After receipt of fMDA Round 1a, Hb and urine testing will be conducted on the same day between days 3 and 7 post first treatment with either PQ or TQ [8]. Hb testing will be conducted using the Hemocue portable spectrophotometer per manufacturer’s instructions [8]. Participants and their caretakers will be made aware of possible AE and associated potential symptoms. They will be instructed to act without delay given the possible severity of some events.

For hemolytic events or other severe AEs, participants will be transported within 4 h to the hospital in Iquitos where blood transfusion therapy and other tertiary care is available. Any participant that has any severe adverse reaction associated with any study drug will be withdrawn from receiving further study drug. The participant will continue to be followed as per protocol except will not receive any additional doses of study medication.

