### Monitoring and auditing

A fully independent data safety monitoring board (DSMB) will oversee the progress and safety of the study. The board includes a chair with expertise in cluster randomized controlled clinical trials, as Scientist with expertise in malaria, a biostatistician with expertise in clinical trials, and a local Scientist with experience in data and safety monitoring of trials. The DSMB will be included in discussions prior to the start of the trial to review the analysis plan and will meet approximately annually throughout the trial to advise on study progress. The DSMB may decide to withdraw clusters or participants, including cessation of activities for those clusters or participants. Should early evidence of intervention safety problems arise, the DSMB will advise on stopping the study. The study will be halted if > 11/1000 individuals have incidence of any SAE, including by not limited to AHA, related to taking an 8-aminoquinoline. This stopping rule is based on WHO safety threshold guidelines [1].

Both an internal monitor and an external monitor will oversee the clinical trial. The external monitoring agency will conduct regular site visits including to the laboratory. The internal monitor will help develop a detailed monitoring plan including when/how to review patient charts, who will conduct monitoring visits, and who will address findings from monitoring.

The FLAME study team holds regular meetings to communicate about study progress and procedures. The study data management team meets monthly to monitor data quality. The entire study team holds meetings approximately quarterly.

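### The only stated between-arm safety comparison counts all-cause SAE or severe malaria under fMDA but severe malaria alone in control, so its ratio exceeds 1 with no drug effect

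*Protocol article*

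**What the plan says.** All statements are from the protocol article.

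- *Safety and tolerability analysis*, definition: "Serious adverse events refer to any expected or unexpected event, related or unrelated to the study medication", where the event "results in death, a life-threatening event, hospitalization, prolongation of hospitalization, disability or incapacity, or a congenital anomaly". The definition covers all causes.
- Same section, one-arm measure: "The incidence of serious adverse events (SAE) from fMDA, defined as SAEs divided by person-time at-risk, will be measured".
- Same section, between-arm comparison: "The incidence of SAE or severe malaria in fMDA will also be compared to the incidence of severe malaria in the control arm".
- *Safety*: "Monitoring for this AESI and other adverse reactions will be conducted through passive and active surveillance being conducted in both study arms". That section also has study staff asking about adverse events at monthly visits.
- *Monitoring and auditing*: the stopping rule counts "any SAE, including by not limited to AHA, related to taking an 8-aminoquinoline". Of the places where SAEs are counted, this is the only one with an explicit relatedness limit.

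No other section states a comparison of SAEs between arms.

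**The concern.** The endpoint itself differs by arm. A death, an unrelated hospital admission or a congenital anomaly in an fMDA community enters the comparison; the same event in a control community does not. Randomization balances the underlying risks but cannot correct for events that are counted on one side only.

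The overall objective in *Aims and objectives* is impact and safety compared with no fMDA, so readers will look for a comparative safety result. Most people in low-transmission communities are uninfected, and the *Background* itself says that in such settings the risks of MDA may outweigh its benefits. A contrast that shows excess harm for an inert drug would be a poor basis for that judgement.

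**Working it through.** The article gives no figure for this comparison, so there is none to reproduce. The check is algebra, followed by an illustration with assumed rates.

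**Set-up.** Let b be the rate of SAEs other than severe malaria and m the rate of severe malaria, both per 1000 person-years. Suppose the drug has no effect, so both rates are equal in the two arms.

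- As written: fMDA rate = b + m, control rate = m, ratio = (b + m)/m.
- Same endpoint in both arms: (b + m)/(b + m) = 1.0 for any b and m.

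Severe malaria that is also an SAE counts in both arms. The one-sided part is b alone.

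**Null ratio.** Neither rate is in the article; the values below are assumptions.

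| b | m = 0.5 | m = 1 | m = 2 |
|---|---|---|---|
| 1 | 3.0 | 2.0 | 1.5 |
| 5 | 11 | 6.0 | 3.5 |
| 10 | 21 | 11 | 6.0 |
| 20 | 41 | 21 | 11 |

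**Expected events.** *Sample sizes and power calculations* gives 15 clusters per arm with a mean of 251 people: 15 × 251 = 3765 people per arm. If all are followed, that is 3765 person-years in one year and 3 × 3765 = 11,295 in three.

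- b = 5, m = 1, one year: 6 × 3.765 = 22.6 events under fMDA against 1 × 3.765 = 3.8 in control.
- b = 5, m = 1, three years: 67.8 against 11.3.
- b = 1, m = 2, one year: 11.3 against 7.5. Three years: 33.9 against 22.6.

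**Chance of a false harm signal.** Poisson counts were simulated with no drug effect and tested with a two-sided conditional exact test at 0.05, ignoring clustering. At b = 5, m = 1, a significant excess under fMDA appeared in about 97% of simulations for one year and about 100% for three. At b = 1, m = 2, it appeared in about 10% and 28%.

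**If fMDA prevents severe malaria.** With rates m0 in control and m1 under fMDA, the ratio as written is (b + m1)/m0. It falls below 1 only if b is less than m0 − m1, that is, if the severe malaria prevented exceeds all other background SAEs. Suppose severe malaria fell by 68%, the reduction in incidence on which the trial is powered (that severe malaria would fall in proportion is an assumption). With b = 1 and m0 = 2, m1 = 0.32 × 2 = 0.64. The ratio as written is 1.64/2 = 0.82; on the common endpoint it is 1.64/3 = 0.55. With b = 5 and m0 = 1, the ratio as written is 5.32/1 = 5.3, against 5.32/6 = 0.89.

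**The case against.** The strongest defence is that this is a deliberate net-harm contrast: harm caused by the drug plus remaining severe malaria, set against severe malaria without the drug. The preceding sentence speaks of SAEs arising from fMDA, which hints at attribution, and the comparison cites sources that cannot be seen here. That contrast would be coherent, but only with fMDA-arm SAEs limited to drug-related ones. The definition in the same paragraph says "any expected or unexpected event, related or unrelated to the study medication", and the stated rate is simply SAEs over person-time at risk. The authors did write a relatedness limit into the stopping rule; the comparison has none. The defence may explain the intent, but the text still needs correcting.

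Other objections stand and limit the point. A reader might go further in four ways that the article does not support:

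- *That all background SAEs count against fMDA alone.* Severe malaria meeting the SAE definition counts in both arms.
- *That control would contribute no events.* At an assumed 2 unrelated SAEs per 1000 person-years, 11,295 × 0.002 is about 23, and 23 against 0 on a sign test gives 2 × 0.5^23 = 2.4 × 10⁻⁷. This omits control-arm severe malaria and ignores clustering. It also takes whole-population follow-up for three years, whereas the article does not say whose time is at risk, and treatment reaches only eligible people near index cases. The article names no test for this contrast either.
- *That control-arm SAEs will go unreported.* Surveillance runs in both arms, adverse events are to be described, and tables by arm may well be in an analysis plan that is not shown.
- *That the whole risk-benefit conclusion fails.* Safety is listed as a secondary aim and is measured mainly by adverse event incidence. The SAE rate under fMDA, the analyses by drug, and the haemoglobin and urine testing do not depend on this contrast.

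**Conclusion.** The point holds for one secondary safety contrast. As written, the two arms are measured on different endpoints, and the expected ratio with no drug effect is (b + m)/m. This exceeds 1 whenever any background SAE other than severe malaria occurs. Over the assumed rates it runs from 1.5 to 41, against 1.0 on a common endpoint.

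The direction and the formula follow from the article's own definitions. The size rests on assumed rates, and the event counts also rest on full follow-up of 3765 people per arm. A narrower at-risk population would lower the counts without removing the mismatch. The false-signal percentages ignore clustering and are illustrative.

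The bias runs against fMDA, so it would tend to overstate harm rather than hide it. The primary efficacy result is untouched, and so is the stopping rule, which counts related events.

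**What to change.** Define the same endpoint in both arms: incidence of any SAE, including severe malaria, per person-time, over the same population and follow-up, with allowance for clustering. Report severe malaria against severe malaria as a separate comparison.

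If a net-harm contrast is also wanted, limit the SAEs added in the fMDA arm to those judged drug-related and label the contrast as net harm. Attribution is subjective in an open-label trial, so the all-cause comparison should be the main one.

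The cost is a change of wording in the protocol or analysis plan. The surveillance described for both arms should already supply the control-arm events; the team should confirm that SAEs are ascertained and recorded in the same way in control communities.
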